### Participants

The study will include 65 mTBI participants and 65 control subjects for the cross-sectional arm of the study. All subjects will be between the ages of 18 and 60. Participants in the mTBI group will have a diagnosed mTBI or concussion and chronic, non-resolving complaints of balance problems determined by a score >0 on the Dizziness Handicap Inventory (DHI) at the time of testing and > 3 months post-injury. Control subjects will be gender and age matched to the mTBI group. For the second arm of the study, a subset of 40 mTBI subjects with abnormal central sensorimotor integration with or without peripheral vestibular or ocular motor deficits will be randomized into two rehabilitation groups, experimental treatment and standard of care, consisting of two rehabilitation sessions per week for 6 weeks. All subjects will be tested at either Oregon Health & Science University or the VA Portland Health Care System. All rehabilitation will take place at Oregon Health & Science University. Informed written consent will be obtained from all participants.

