### Study 1: Characterization of balance deficits

#### Assessment procedures

All people who are eligible per phone screening will come into the clinic for the informed consent process. An investigator will verbally explain the consent form, allow the person ample time to read through the consent form and then will acknowledge consent by signing the form. All subjects will first read and sign consent forms. For study 1, 65 mTBI participants and 65 control subjects will be assessed on a battery of tests designed to measure vestibular function, sensorimotor integration, static and dynamic balance, cognition, reaction time, clinical sensory loss, and self-reported symptoms. All protocols have been approved by the OHSU Institutional Review Board.

Participants will complete a novel central sensorimotor integration test (CSMI test) [22] on a modified research NeuroCom platform using custom-designed, low-amplitude (2° and 4° peak-to-peak) pseudorandom stimuli that apply continuously repeated cycles of wide bandwidth surface-tilt and/or visual-tilt stimuli with individual tests lasting ~5 min. The participants’ anteroposterior (AP) body displacement at shoulder and hip levels, and surface and visual surround rotation angles will be recorded. Subjects will perform 8 trials (2 amplitudes x 4 test conditions) in one session with trials presented in a randomized order and interspersed with rest breaks (Table 1). Anthropometric measures will be obtained for the purpose of estimating body mechanics needed for later analysis (moment of inertia, mass, height of center of mass, CoM) [22].

**Table 1 Tab1:** Aim 1 CSMI test conditions and sensory weight comparisons

Condition	Vision	Support Surface	Visual Surround	Sensory Weight Comparisons
1	EC	PRS	--	*W* _*prop*_ vs. *W* _*vest*_
2	EO	PRS	Fixed	*W* _*prop*_ vs. *W* _*vis*_ *+ W* _*vest*_
3	EO	Fixed	PRS	*W* _*vis*_ vs. *W* _*prop*_ *+ W* _*vest*_
4	EO	PRS	PRS	*W* _*prop*_ *+ W* _*vis*_ vs. *W* _*vest*_

*EC* eyes closed, *EO* eyes open, *PRS* pseudorandom stimulus

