#### Primary outcome measure

The primary outcome measures of central sensorimotor integration are the parameters derived from a model-based interpretation of CoM sway evoked by pseudorandom stimuli (Table 2). The procedure for calculating these parameters is to (1) calculate CoM angular displacement from experimental measures of hip and shoulder displacement on each test trial, (2) use Fourier methods to calculate a frequency response function, FRF (e.g. Fig. 2d) [46], and (3) adjust parameters of a model of the balance control system represented by the Fig. 2a block diagram using a constrained optimization algorithm (Matlab “fmincon” function; The Mathworks, Inc., Natick, MA) until the model-derived FRF optimally matches the experimental FRF (e.g. model-derived FRFs in Fig. 2d) [22, 47]. This analysis procedure will be applied to each of the 8 individual tests performed by each subject. The full set of model parameters are defined in Table 2.

**Table 2 Tab2:** Balance control model parameters

*W* _*vis*_ *, W* _*prop*_ *, W* _*vest*_	Sensory weights of visual, proprioceptive, and vestibular contributions
*K* _*p*_ *, K* _*d*_	Neural controller parameters (sensory-to-motor transform)
*K* _*t,*_	Gain constant (torque feedback pathway)
*t* _*d*_	Net feedback time delay

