**Fig. 2 Fig2:**
[figure not shown]
CSMI methods with example data and analysis. (**a**) A feedback control model forms the basis for identifying model parameters (Table 2) that account for experimentally evoked body-in-space (BS) sway, representing angular tilt of the body center-of-mass (CoM), evoked by support surface (SS) and/or visual surround (VS) rotations. (**b**) An example of one cycle of a pseudorandom surface-tilt stimulus that evoked the CoM body sway (averaged across 5 stimulus cycles) shown in (**c**) for a Control subject and TBI subject. (**d**) Frequency domain analysis of stimulus/response data in (**b**) and (**c**) yields frequency response functions (FRFs) expressed as gain (ratio of CoM response amplitude to stimulus amplitude) and phase (timing of response relative to stimulus) measures as a function of frequency components in the pseudorandom stimulus. Parameters of the model in (**a**) are calculated by a fit procedure that finds parameters that optimally account for the FRF gain and phase data

The parameters include sensory weights that represent the relative contributions of proprioceptive, visual, and vestibular sensory information to balance control such that in each of the 4 test conditions the sum of weights equals 1. These weights are known to vary with test conditions that alter the availability (e.g. eyes open or closed) or reliability (e.g. varying stimulus amplitudes) of sensory information and are affected by sensory abnormalities (22, 24). For condition 1 tests (surface tilt stimulus with eyes closed) the model fit to the experimental FRF provides a measure of the proprioceptive contribution (Wprop). With eyes closed, the visual contribution (Wvis) is zero and therefore the vestibular contribution is Wvest = 1 – Wprop. Condition 2 tests also use a surface tilt stimulus but eyes are open with both visual and vestibular cues providing accurate orientation information. The model fit again provides an estimate of Wprop but now 1 – Wprop = Wvis + Wvest. Condition 3 tests present a visual tilt stimulus where the model fit provides a measure of Wvis and 1 – Wvis = Wprop + Wvest. Finally condition 4 tests simultaneously present the same surface and visual-tilt stimulus. In this condition the model fit provides a measure of Wprop + Wvis with Wvest = 1 – (Wprop + Wvis).

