#### Clinical testing for classification and covariates

To classify mTBI participants as with or without vestibular dysfunction, standard vestibular testing will be performed as described in Table 4. Clinical tests to examine potential covariates of sensory loss will also be included at the initial visit in Study 1.

**Table 4 Tab4:** List of clinical sensory and vestibular tests for classification and covariates / comorbidities of primary and secondary outcomes

Domain Tested	Test	Description	Positive Result
Sensory	Proprioception test	Assess the ability of the participant to detect the position of the great toe or ankle as it is moved by a researcher / clinician	Unable to detect changes in position
	Visual Vertical Test	Requires participant to orient a line to vertical and quantifies the deviation from vertical	Falls outside control group mean ± 2 SD
Ocular Motor	Saccadic Latency	Assesses the ability to make a rapid eye movement, latency would be the time it takes to initiate a saccade (eye movement) after the target has moved	Falls outside control group mean ± 2 SD
	Gaze	Assesses the ability to maintain stable vision on a fixed target.	
	Smooth Pursuit	Assesses the ability to accurately track/follow a moving/sinusoidal target with the eyes.	
	Convergence	Assesses the ability to view a close target without double vision	
Vestibular	cVEMP	Neurophysiological test assessing the function of the saccule	Falls outside control group mean ± 2 SD
	oVEMP	Neurophysiological test assessing the function of the utricle	
	Caloric	Assesses function of the lateral semi-circular canals and superior branch of the vestibular nerves	
	Head Impulse	Assesses function of semi-circular canals and vestibular nerve branches, specifically the lateral canals/superior vestibular nerve	

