#### Statistical analysis

To determine if objective/novel measures of balance will better distinguish people with mTBI from control subjects than clinical measures, we will use logistic regression classification models. Improvements in classification will be determined by calculating the area under the curve (AUC) of the receiver-operator characteristic and then comparing AUC for each traditional clinical measure with the novel objective measures. Significance will be assessed using bootstrapping to determine if the observed differences in AUC are greater than would be expected by chance at a level of 0.05.

To determine if a subset of people with mTBI will have abnormal CSMI test measures, even without peripheral vestibular or ocular motor deficits, we will use descriptive statistics to characterize the distribution of CSMI test measures and vestibular/ocular motor scores. We will define CSMI test measures and vestibular/ocular motor scores as abnormal if the scores are greater than 2 standard deviations from the mean in controls. We will then classify mTBI subjects into one of 4 CSMI-vestibular/ocular motor categories 1) abnormal CSMI –abnormal vestibular/ocular motor scores, 2) abnormal CSMI –normal vestibular/ocular motor scores, 3) normal CSMI –abnormal vestibular/ocular motor scores, 4) normal CSMI –normal vestibular/ocular motor scores.

To determine if the observed relationship between poorer static/dynamic balance performance and mTBI is regulated/mediated by central sensorimotor integration, we will use mediation analysis. Mediation analysis [49] will allow for the partitioning of the association between mTBI and chronic imbalance into two parts, the direct relationship of mTBI on balance impairment as well as the causally mediated effect of mTBI on central sensorimotor integration, which, in turn is having the actual effect on imbalance. These varying generative mechanisms of balance deficits will be assessed by utilizing linear models relating mTBI to CSMI test measures alongside models of mTBI and CSMI test measures jointly affecting imbalance using the apportionment methods described by Baron and Kenny [49].

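### The plan never says how up to 40 CSMI values or 8 vestibular/ocular tests make a person abnormal, and it does not classify controls, so chance alone can appear to support Study 1 hypothesis b

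*Protocol article*

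**What the plan says.** **Cut-off.** The protocol article (Study 1, Statistical analysis) states, with the controls as reference: "We will define CSMI test measures and vestibular/ocular motor scores as abnormal if the scores are greater than 2 standard deviations from the mean". Table 4 gives the matching criterion for the ocular motor and vestibular tests: "Falls outside control group mean ± 2 SD".

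**Person-level label.** The same paragraph then sorts mTBI subjects into four categories, crossing CSMI abnormal or normal with vestibular/ocular abnormal or normal. It names no parameter or trial, minimum count, composite or error rate that would lead from flagged measures to a flagged person. The categories are applied to mTBI subjects only.

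**Number of measures.** Study 1, Assessment procedures: "Subjects will perform 8 trials (2 amplitudes x 4 test conditions) in one session". Under Primary outcome measure, the model fit is separate for each trial: "This analysis procedure will be applied to each of the 8 individual tests performed by each subject". The parameters are those of Table 2, and the text after Fig. 2 adds that "in each of the 4 test conditions the sum of weights equals 1".

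**Use of the label.** Hypothesis b (Background) is that some people with mTBI have abnormal CSMI without a peripheral vestibular or ocular motor deficit. The Discussion draws its conclusion about impaired central integration if some unspecified share of subjects shows this pattern. Participants makes the same label the entry condition for Study 2: "a subset of 40 mTBI subjects with abnormal central sensorimotor integration".

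**The concern.** A 2 SD cut-off has a known false-positive rate for one measure. Once many measures feed one label, the rate for the person depends on how they are combined, and the plan does not fix that step. Depending on the rule chosen, the label could mark nearly everyone or almost no one.

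Two things are at stake. First, hypothesis b has no benchmark. It is judged by whether a category is occupied, and some healthy people would occupy it too. With no control classification, the reader cannot tell a deficit from the expected tail of a normal distribution. Second, Study 2 is meant for people with a CSMI deficit and is powered on improvement in that deficit. If the label is loose, some of those randomised have no deficit to improve.

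**Working it through.** The plan states no false-positive rate for this rule, so there is no figure to reproduce. The check asks what rate the rule implies in people with no deficit.

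**Inputs from the document**
- CSMI trials: 8, each fitted separately.
- Free parameters per trial: one sensory weight or weight sum (the weights sum to 1), plus Kp, Kd, Kt and td, making 5. CSMI values per person: 8 x 5 = 40.
- Vestibular/ocular tests in Table 4: 4 ocular motor + 4 vestibular = 8, taking the 2 SD criterion to cover all tests in each of the two domains.
- Sample: 65 mTBI and 65 controls in Study 1; 40 mTBI in Study 2.

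**Assumptions not in the document:** normal scores, a two-sided cut-off unless stated, and the correlations below.

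**Step 1: one measure.** 2 x (1 - Φ(2)) = 0.0455 two-sided; 0.0228 one-sided.

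**Step 2: any one value suffices, independent values.** The rate is 1 - (1 - 0.0455)^k.
- k = 40: 84.5% (one-sided 60.2%).
- k = 8: 31.1%.
- With the mean and SD estimated from 65 controls (t prediction, per-measure rate 0.0515): 87.9% and 34.5%.

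**Step 3: any one value suffices, correlated values.** Simulation of 100,000 healthy people, two-sided:

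| Correlation within a parameter across trials / between parameters | CSMI flagged |
|---|---|
| 0.3 / 0 | 80% |
| 0.5 / 0 | 73% |
| 0.5 / 0.2 | 70% |
| 0.7 / 0 | 62% |
| 0.7 / 0.3 | 56% |
| 0.5 / 0.5 | 54% |
| 0.8 / 0.5 | 43% |
| 0.7 / 0.7 | 35% |
| 0.9 / 0.9 | 17% |

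For the 8 vestibular/ocular tests the rate is 28%, 23% and 18% at correlations of 0.3, 0.5 and 0.7.

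**Step 4: other rules the text would allow** (independent values)
- One trial only, 5 parameters: 1 - 0.9545^5 = 20.8%.
- Only the two parameter-conditions used for Study 2 power: 1 - 0.9545^2 = 8.9%.
- At least 2, 3, 4 or 5 of 40: 54.9%, 27.4%, 10.7%, 3.4%.

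Count rules also shift with correlation: at least 4 of 40 flags 10.7% if independent but 18.5% at 0.7 / 0.

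**Step 5: the category behind hypothesis b, in the case most favourable to the plan.** Take one CSMI measure only, no deficit, and an any-one rule for 8 independent vestibular/ocular tests that are also independent of CSMI.
- Probability of CSMI abnormal with vestibular/ocular normal: 0.0455 x (1 - 0.311) = 0.0313.
- Expected among 65: 65 x 0.0313 = 2.0.
- Probability of at least one: 1 - (1 - 0.0313)^65 = 87%.
- With a one-sided CSMI cut-off: 0.0228 x 0.689 = 0.0157, so 1.0 expected and a 64% chance of at least one.

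At the other extreme (any one of 40, independent): 0.845 x 0.689 = 0.582, or about 38 of 65.

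**Step 6: Study 2 entry.** It needs 40/65 = 62% of the mTBI cohort. Under any-one with independent values, 65 x 0.845 = about 55 people without a deficit would qualify.

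**The case against.** **The any-one rule is not in the text.** This is correct. A reader might infer that the plan flags 84% of healthy people, but the document does not say that one outlying value is enough, and Step 4 shows that other rules give far lower rates. The 84.5% also assumes independence. The parameters of one trial come from one fit to one response function, so some correlation between them is plausible, and the document gives none. With strong correlation, or a one-sided cut with moderate correlation (38% at 0.5 / 0.2), the rate is below half.

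**Flagging most healthy people is not true of both batteries.** This is also correct. For the vestibular/ocular tests, the two-sided calculations above give about 18% to 34%.

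**A condensed article leaves such rules to the full protocol.** This stands in part. The exact algorithm could be elsewhere. But the article itself states the cut-off, the categories, the entry condition and the inference to be drawn, restricts the classification to mTBI subjects, and sets no benchmark share. Step 5 shows that this inference is exposed to chance even if only one measure counts.

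**Hypothesis b is descriptive, and other analyses compare mTBI with controls.** There is no significance test to inflate, and the AUC and mediation analyses do use controls. Neither addresses abnormal CSMI in people with normal vestibular/ocular results, which rests on the four-way table alone.

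**A loose entry filter invalidates Study 2.** A reader might infer this, but the documents do not support it. Both arms are drawn by randomisation from the same entrants, so the comparison stays unbiased. Only the target population and the expected effect are diluted, in what the article calls a pilot.

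**Conclusion.** The concern holds in this form: the plan fixes a cut-off per measure and a label per person but not the step between them, and it does not apply the label to controls. The false-positive rate of the CSMI label is therefore undetermined. Among the rules the text allows, it runs from 3.4% (at least 5 of 40) to 84.5% (any one of 40) with independent values. Under any-one alone it runs from 17% to 84.5% over the assumed correlations. These figures rest on normal scores and a two-sided cut-off.

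The consequence for hypothesis b depends least on the missing rule. With a single CSMI measure and no deficit, about 2 of 65 people would be expected in the deciding category, with an 87% chance of at least one (about 1 person and 64% if one-sided). Finding some such people is therefore not evidence of a central deficit unless their share exceeds that in controls. For Study 2 the consequence is possible dilution, of unknown size, not bias.

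**What to change.** 1. **State one person-level CSMI rule with a controlled false-positive rate in controls.** Options are pre-named parameters and trials, a minimum count, or a composite cut at the control 95th percentile with controls scored leave-one-out. A composite should keep the conditions apart: the fitted weight is proprioceptive in conditions 1 and 2, visual in condition 3 and their sum in condition 4, so a plain average over the 8 trials would mix different quantities. A count rule should be calibrated on the controls, since its rate depends on the correlations. For scale, with independent values an any-one rule would need a cut-off of about 3.22 SD for 40 values to hold 5%.
2. **Do the same for the vestibular/ocular battery** (about 2.73 SD for 8 independent tests under an any-one rule).
3. **Freeze the rule and its cut-off before Study 2 randomisation starts**, and keep all randomised people in the analysis if later control data would move the cut.
4. **Apply the four-way classification to the 65 controls**, and base hypothesis b and the matching Discussion conclusion on the mTBI share exceeding the control share.

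The cost is a few sentences and one extra table from data already planned for collection. Two drawbacks should be acknowledged. Fewer people may qualify for Study 2, so recruitment may be slower. A 95th percentile from 65 controls rests on about 3 people (0.05 x 65 = 3.25), so the cut will be imprecise and should be reported as such.

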### Study 2: Rehabilitation of balance deficit

#### Assessment procedures

Subjects with mTBI who participate in Study 1 will be screened for Study 2. An investigator will verbally explain the consent form and time commitments involved with the rehabilitation, allow the person ample time to read through the consent form and then will acknowledge consent by signing the form. For Study 2, 40 mTBI participants will participate in a 6-week rehabilitation program randomized to either 1) a standard vestibular focused rehabilitation program or 2) the same standard vestibular focused rehabilitation program with the addition of audio biofeedback. Post-rehabilitation assessments will be conducted one week after the conclusion of the program. Retention will be assessed 6 weeks following the post-rehabilitation session. A flowchart illustrating the study design is depicted in Fig. 3.

**Fig. 3 Fig3:**
[figure not shown]
Flowchart illustrating the study design. Study 1 is a cross-sectional design. Study 2 recruits subjects from Study 1 for a randomized intervention

#### Intervention

Participants will be randomized into either 1) a standard of care vestibular rehabilitation program or 2) a standard or care vestibular rehabilitation plus ABF training program. Rehabilitation will begin approximately 7-10 days after pretest assessment. Both groups will receive the rehabilitation that includes progressive (3 levels of difficulty) exercises that target gaze stabilization, vestibular stimulation, balance and proprioceptive retraining [50–52] (Table 5). Subjects randomized to the ABF training, will undergo the same vestibular rehabilitation program but will wear an ABF device while performing the rehabilitation exercises. All researchers performing post-rehabilitation testing will remain blinded to the randomized group assignment throughout the duration of the study.

**Table 5 Tab5:** Rehabilitation protocol

Exercise	Vision	Surface	Time	Progression	ABF
Static Balance	Eyes open	Firm	30 s per condition	10 double stance conditions including tossing a ball, head rotations left-right, head rotations up-down, head rotations with smooth pursuit, with gaze stabilization, and with saccades	Pitch modulated feedback for AP sway, direction modulated for ML sway
	Eyes closed	Firm	30 s per condition	3 double stance conditions including head rotations left-right, head rotations up-down	
	Eyes open	Foam	30 s per condition	4 double stance conditions including tossing a ball, head rotations left-right, head rotations up-down	
	Eyes closed	Foam	30 s per condition	3 double stance conditions including head rotations left-right, head rotations up-down	
Dynamic Balance (Tandem Gait)	Eyes open	Firm	30 s per condition	4 tandem gait conditions including tossing a ball, head rotations left-right, head rotations up-down	Direction modulated for ML sway
	Eyes closed	Firm	30 s per condition	1 tandem gait condition	
	Eyes open	Foam	30 s per condition	4 tandem gait conditions including tossing a ball, head rotations left-right, head rotations up-down	
	Eyes closed	Foam	30 s per condition	1 tandem gait condition	
Dynamic Balance (Bending down)	Eyes open	Firm	30 s per condition	3 different heights	Direction modulated for ML sway
	Eyes closed	Firm	30 s per condition	3 different heights	
Dynamic Balance (Squatting)	Eyes open	Firm	30 s per condition	4 squats including sit-to-stand, lunge, lunge onto unstable surface, and lunge + twist	Direction modulated for ML sway
	Eyes closed	Firm	30 s per condition	4 squats including sit-to-stand, lunge, lunge onto unstable surface, and lunge + twist	
	Eyes open	Foam	30 s per condition	4 squats including sit-to-stand, lunge, lunge onto unstable surface, and lunge + twist	
	Eyes closed	Foam	30 s per condition	4 squats including sit-to-stand, lunge, lunge onto unstable surface, and lunge + twist	

